### 2.2. Recruitment of Participants

Patients attending their specialist examination appointments will be advised about the study by physicians. Physicians will identify potentially eligible patients and will initiate discussion of the study with them. After discussion with physicians, interested patients will be asked to book an appointment on one of the pre-determined recruitment days to speak to a research assistant about the study. During the scheduled appointment, the research assistant will explain the different phases of the study and will obtain informed consent from patients who will agree to participate.

### 2.3. Eligibility

All participants will have to meet the following eligibility criteria: 18 years of age or older; diagnosis of essential arterial hypertension (SBP ≥ 140 mmHg and/or DBP ≥ 90 mmHg, evaluated in the standard way or by 24-h mean arterial pressure (MAP) value monitoring) or ACS; able to complete the study measures and interventions in Italian; without other serious diseases (such as cancer) or psychiatric disorders that could compromise the participation in the study.

### 2.4. Measures

For an overview of all measures over the different measurement time points, please see Table 1. The background variables that will be assessed both at baseline and at the six-month follow-up are explained in the following paragraphs. 

#### 2.4.1. Dietary Behavior

To measure dietary behavior, a modified version of the Mediterranean Diet Scale (MDS), [28] will be used. The instrument measures the weekly consumption of nine foods using a six-point Likert scale, where 1 indicates “Never” and 6 indicates “More than three times a day”. The consumption of both beneficial (i.e., vegetables, fruits, whole grains, fish, legumes, olive oil, up to two glasses of wine per day) and detrimental foods (i.e., more than two glasses of wine per day, butter and margarine, red or processed meat) will be assessed. Each response is recoded into a dichotomous variable according to Trichopoulou et al. [28], where 1 indicates healthy and 0 indicates unhealthy consumption. The sum of the recoded responses yields the Mediterranean Diet Scale (MDS) score, on which higher scores indicate a healthier diet. 

#### 2.4.2. Physical Activity

Physical activity will be measured with the Rapid Assessment of Physical Activity-1 (RAPA-1) [29], a self-report instrument to assess physical activity in clinical contexts [30,31,32]. The RAPA consists of seven hierarchical questions about different intensity levels and frequency of physical activity and aerobic exercise. The intensity levels of the activity (light, moderate, vigorous) are described and examples of them are given. Each question requires a dichotomous (yes/no) response, where “yes” is scored 1 and “no” is scored 0. The total score is obtained by adding the scores of individual items and it ranges from 1 (“I rarely or never do any physical activity”) to 7 (“I do 20 min or more of vigorous physical activity a day, three or more days a week”). 

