#### 2.6.1. Change in Lifestyle Habits

The primary outcome will be the change in behaviors, as measured six and 12 months after baseline. Changes in diet, physical exercise, alcohol intake, and smoking behavior will be evaluated singularly.

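### Physical activity, one of the four primary behaviors, is scored by a sum of seven yes/no items that does not fit its own 1–7 range and anchors

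*Protocol article*

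**What the plan says.** Section 2.4.2 describes the instrument and its scoring in four steps:

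- Structure: "The RAPA consists of seven hierarchical questions about different intensity levels and frequency of physical activity and aerobic exercise".
- Item coding: "Each question requires a dichotomous (yes/no) response, where “yes” is scored 1 and “no” is scored 0".
- Total: "The total score is obtained by adding the scores of individual items and it ranges from 1".
- Anchors: "it ranges from 1 (“I rarely or never do any physical activity”) to 7", and at the top "to 7 (“I do 20 min or more of vigorous physical activity a day, three or more days a week".

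The article gives no list of the seven items, no reverse coding of the inactivity statement, and no rule that takes the highest item affirmed.

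Section 2.6.1 makes this score a primary endpoint: "The primary outcome will be the change in behaviors, as measured six and 12 months after baseline". It adds: "Changes in diet, physical exercise, alcohol intake, and smoking behavior will be evaluated singularly". Section 2.9 plans repeated-measures ANOVA and regression for the behavior changes, with the baseline value as covariate.

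**The concern.** The anchors are first-person statements that a patient would agree or disagree with, placed at the two ends of a ladder. They describe a level: where on the ladder the patient stands. The scoring sentence describes a count: how many statements the patient agrees with. When one of the statements says that the patient is inactive, the two are different quantities, because agreeing with it adds a point to an activity total and disagreeing with it removes one.

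Physical activity is evaluated on its own, so no other component of the primary outcome would correct a mis-scored value. Scoring syntax written from this sentence would give values that do not match the scale printed beside it, and a reader of the results could not tell which scale was used.

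**Working it through.** **Inputs (all from section 2.4.2).** Seven items; yes = 1, no = 0; total = sum; stated range 1 to 7; score 1 labelled with the inactivity statement; score 7 labelled with the vigorous-activity statement. The inactivity statement is taken to be item 1 and the vigorous statement item 7. This is inferred from the anchors, since the items are not listed.

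**Step 1. The stated range under the stated rule.** Minimum = 7 × 0 = 0; maximum = 7 × 1 = 7. The plain sum runs 0–7, so the stated lower limit of 1 is not reproduced. This step needs no assumption about item content.

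**Step 2. What a total of 7 requires.** There are 2^7 = 128 answer patterns. Exactly one totals 7: yes to every item. If the inactivity statement is an item, that patient has affirmed both being rarely or never active and exercising vigorously.

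**Step 3. Consistent answers.** Let item 1 be affirmed exactly when items 2–7 are all answered no. That leaves 2^6 = 64 patterns.

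- The range of the sum is 1–6.
- A total of 1 arises from 1 inactive pattern and from 6 active patterns (one for each of items 2–7 affirmed alone). One of these six is the vigorous item alone, which the anchors place at 7.
- Under a weaker restriction, where item 1 excludes only item 7, the range is 0–6. The top anchor is still out of reach.

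**Step 4. Consistent and cumulative answers.** A patient at level k ≥ 2 answers no to item 1 and yes to items 2 through k, so the sum is k − 1. The inactive patient scores 1.

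| Level on the anchors | 1 | 2 | 3 | 4 | 5 | 6 | 7 |
|---|---|---|---|---|---|---|---|
| Sum as written | 1 | 1 | 2 | 3 | 4 | 5 | 6 |
| Highest item affirmed | 1 | 2 | 3 | 4 | 5 | 6 | 7 |

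Moving from level 1 to level 2 changes the sum by 1 − 1 = 0. Every later step changes it by 1. The sum would return 1–7 on cumulative answers only if every patient, including the vigorous exerciser, affirmed item 1, and its wording does not allow that.

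**Step 5. Non-cumulative answers.** A patient who affirms items 2, 3 and 4 at baseline (sum 3) and only item 7 later (sum 1) has risen from level 4 to level 7 while the sum fell by 2. This shows what the rule permits, not how often it would happen.

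**Step 6. Sample size (section 2.7).** With f = 0.10, three groups, three measurements and correlation 0.5, λ = f²·N·m/(1 − ρ) = 0.01 × 204 × 3 / 0.5 = 12.24, with df = (3 − 1)(3 − 1) = 4 and (204 − 3)(3 − 1) = 402. Power is 0.806. The smallest N reaching 0.80 is 202, or 204 in equal arms. The stated 204 reproduces, and the scoring of this instrument does not enter it.

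**The case against.** Several points on the other side have weight.

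- **The items are not listed.** This stands as a limit: everything beyond step 1 rests on the inactivity statement being one of the seven. The inference is strong, because under a 0/1 sum a score of 1 means exactly one yes, and the label of that score reads as the statement affirmed.
- **The range can be reached.** A reader might infer that 1–7 is simply unattainable. It is not: a score of 1 is reachable, and 7 is arithmetically reachable, though only through contradictory answers.
- **The questions are called hierarchical.** Under cumulative answering the sum still ranks patients, with one tie at the bottom, and no gain lowers the score. A reader might infer that the score fails to order patients at all, but step 4 does not support that. Reversals and larger ties need non-cumulative answers, for which the document gives no frequency.
- **It may be a slip of description.** The instrument is used by citation and the article is condensed, so the team may intend the level score. That is quite possible, but it does not remove the point. The article does not leave the rule to a fuller document; it states one, and that rule conflicts with the scale in the same sentence.
- **Nothing is lost.** The items are collected at all three time points whichever rule is used, so the correct score can be computed later. This stands, and it makes the correction cheap.

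**Conclusion.** The concern holds as an internal contradiction in the scoring of one of four separately evaluated primary behaviors. The additive rule gives 0–7 without restriction, or 1–6 with consistent answers, against a stated 1–7. It cannot place a consistent vigorous exerciser at the anchor of 7. With cumulative answers the visible cost is one lost step, from inactivity to the lowest active level, and a ceiling of 6. With non-cumulative answers an active patient can also score 1.

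Beyond the 0-versus-1 minimum, this assumes that the inactivity statement is an item. A reader might go further and infer that the treatment effect is biased toward zero or that the result is uninterpretable. The document does not support either: the effect on the comparison between groups depends on response patterns it does not report. Some loss of sensitivity is plausible, especially if many patients start inactive, but its size is unknown.

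**What to change.** In section 2.4.2, replace the scoring sentence with: *The score is the number of the highest-ranked item answered yes (1 to 7).* This reproduces the stated range and both anchors. Use that level as the physical-activity endpoint in the analysis already planned in section 2.9, with baseline as covariate; no new model is needed.

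The cost is one sentence and a change to the scoring syntax, made before any scoring. The questionnaire, the data collected and the sample size of 204 stay as they are.

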#### 2.4.3. Alcohol Intake

The total alcohol intake for each participant will be computed as the mean of the contribution from beer (1 = “I don’t drink beer”, 2 = “Up to two glasses a day”, 3 = “three or four glasses a day”, 4 = “More than four glasses a day”), wine (1 = “I don’t drink wine”, 2 = “Up to 2 glasses a day”, 3 = “Three or four glasses a day”, 4 = “More than four glasses a day”), and spirits (1 = “I don’t drink spirits”, 2 = “One glass occasionally—a few times a year”, 3 = “one glass habitually—e.g., every week, always after meals, etc.”, 4 = “More than one glass habitually—e.g., every week, always after meals etc.”), as used in a previous research [33,34]. 

#### 2.4.4. Smoking Behavior

Smoking behavior will be measured by the Fagerström Test for Nicotine Dependence [35], a six-item scale that evaluates the quantity of cigarette consumption, the compulsion to use, and dependence. The higher the total Fagerström score is, the more intense is the patient’s dependence on nicotine. 

#### 2.4.5. HAPA Constructs

The intervention will be guided by Schwarzer’s Health Action Process Approach (HAPA) model [36,37]. The questions used to measure the HAPA constructs have been developed following suggestions from the authors of the model [36,37].

Risk perception will be assessed using three questions on a 5-point Likert scale, where 1 indicates “Not at all” and 5 indicates “Extremely”. Patients will be asked if and how their lifestyle habits could be dangerous for their health status and how likely they are to have caused their CVDs, from both an individual perspective and in comparison with other people of the same age and gender. Self-efficacy will be investigated by asking participants to assess their ability to adopt a healthier lifestyle on a five-point Likert scale, where 1 indicates “Not able at all” and 5 indicates “Extremely able”. Intention to change will be assessed by asking participants to evaluate the strength of their intention to change their current habits, from “I do not intend to change” to “I strongly intend to change”. Positive and negative outcome expectancies will be investigated by asking the probability of the occurrence of several events if a new healthier behavior is adopted. Both positive and negative expectancies (e.g., “My health would get better”, “My physical appearance would get better”, “Other people would appreciate my willpower”, “It would prevent further cardiovascular diseases”) and negative (“It would take a long time to became a habit”, “I would feel nervous”, “My social life would become worse”) will be measured using a five-point Likert scale, where 1 indicates “Very unlikely” and 5 indicates “Very likely”. The plan to change lifestyle habits will be investigated using a three-point Likert scale question where 1 indicates “I’ve made no plans at all” and 3 indicates “I’ve made a lot of plans”. This will evaluate if patients have made concrete plans about changing their behavior. 

#### 2.4.6. Illness Perception

The brief illness perception questionnaire (Brief-IPQ) [38] is used to measure patients’ perceptions of their disease. The Brief IPQ is a self-report scale of eight-items, five of which assess cognitive illness representations (consequences, timeline, personal control, treatment control, identity) two assess emotional representations (concern and emotions) and one item assesses illness comprehensibility. All the items are measured using a five-point Likert scale.

#### 2.4.7. Needs for Information

Patients’ information needs will be investigated with two questions evaluating the need for further information (in addition to the information already held) in six domains related to the management of hypertension or ACS [27,39]. These domains are: “Pharmacological Treatment”: typology of drugs, how and when to take them, possible side effects;“Knowledge About the Disease”: the anatomical/functional nature connected to the disease (ex. how the blood circulation system functions, what the symptoms connected to the health problem are, and what can be done to manage them);“Daily Activities”: information about everyday activities that can be carried out and which ones have to be modified (ex. work, free time, sexual activity);“Behavioral Habits”: information on lifestyle, with a focus on smoking, diet, alcohol, and physical activity;“Impact of the Disease”: advice on how to manage distress caused by the disease;“Risk and Complications”: the risks related to the disease and possible complications (e.g., the possibilities of a heart attack, how to avoid complications, who to call in case of need, etc.).

The first question asks to “Indicate how much information you would like to receive about the following topics connected to the management of your hypertension”. The answer format is on a five-point Likert scale ranging from 1 (“I want to know nothing about the topic”) to 5 (“I want to know everything about it”). The second question asks to rate the importance of the six domains assigning a value from 1 to 6 (“Now please rate the importance of the topics listed below; you must assign a value from 1 for the most important topic, to 6 for the least important one).

#### 2.4.8. Medical Adherence

Self-reported medication adherence is measured with a modified version (new items were added) of the Self-reported Measure of Medication Adherence [40] at baseline and at six-month follow-up. This adherence measure is designed to facilitate the identification of barriers to and behaviors associated with adequate adherence to chronic medications. Medication adherence scores can range from 0 to 8 with lower scores indicating lower adherence. Medical adherence has been shown to have high concordance with antihypertensive medication pharmacy fill rates in a managed care population similar to the current study population [41].

### 2.5. Intervention

The tailored print intervention will be guided by the HAPA model. This model postulates that people’s health behaviors are determined by different patterns of social-cognitive predictors [self-efficacy, outcome expectancies, and risk perception] that may emerge within two distinguished phases: (1) a goal-setting phase, with pre-intentional motivation processes that lead to a behavioral intention and (2) a goal-pursuit phase, with post-intentional volition processes that lead to the actual health behavior. In the first phase, the formation of an intention to change health behavior commences and is influenced by three factors: risk perception, outcome expectancies, and perceived self-efficacy. In the second phase, the intended behavior has to be initiated and then maintained over the longer term and even restarted in the event of setbacks. As reported in recent reviews [36,42], HAPA has been widely used in research to guide intervention to promote different health behaviors, including diet [43], alcohol consumption [44], and physical activity [45].

In the TTCYB intervention, HAPA is used to identify patients who are located either in the goal-setting phase or in the goal-pursuit phase. Then, each group receives specific messages that are tailored to the group. The basic idea is that individuals pass through different phases on their way to behavior change. Thus, interventions may be most efficient when tailored to these particular phases.

The constructs operationalized as part of the intervention include the intention to change, self-efficacy, outcome expectations, risk perception, adherence to medical treatment, need for information, and patients’ behavior. The messages developed for each phase and construct are presented below.

A library of texts and graphics files has been created to address all the variables on which the messages are customized. The messages were written by a group composed of psychology faculty members and doctoral students, who have experience in research with patients affected by cardiovascular diseases. The content of the messages has been evaluated by specialists who care for patients with chronic disease in clinical settings. Minor revisions were made based on the recommendations of these specialists. After the messages were written, reading levels were assessed and revisions were made if the level was too high. Appropriate pictures were found to enhance the quality of the brochures.

#### 2.5.1. Tailored Group

Participants randomized to the tailored group will receive tailored health material about ten days following the baseline assessment.

The tailored material consists of a nine-page full-color booklet containing a set of information the patients need to know to better manage the disease. The first part of the brochure contains a set of information related to the illness (medical information on the disease and the pharmacological treatment, information on how to manage the distress and the change in life due to the illness, information on the risks and complications of CVDs); the second part is focused on the lifestyle habits (diet, physical activity, alcohol intake, and smoking behavior) that should be modified after a CVD diagnosis.

The two parts are tailored and address different variables. The first part provided personalized information on
Adherence to medical treatment. For example, if a patient answers “yes” to the question “Sometimes if you feel worse when you take the medicine, do you stop taking it?”, he/she will receive a message like “Pay attention, because the treatment for hypertension must not be interrupted without a physician’s approval”.Illness perception. For example, if a patient answers “For a very short time” to the question “How long do you think your illness will continue?”, he/she will receive a message like “Please note that acute coronary syndrome is a chronic disease; this means that it is a long-lasting condition that can be controlled but not cured and you’ll need to take pharmacological treatment for life”.

The second part will be based on
Descriptive feedback on the behavior. For example, “Based on your answers, we determined that your daily consumption of fruits and vegetables is not healthy”. Descriptive feedback is one of the effective strategies used to tailor communication [46], to stimulate patients’ self-referential thought or otherwise focusing attention on specific behaviors related to the outcome of interest.HAPA constructs. In line with HAPA, health messages will be customized to the patients’ intention to change. Specific messages will be developed to address the social-cognitive predictors emerging in the different phases. Patients will be divided into five different stages of changes:Patients who do not intend to change their behavior (non-intenders). This group will be divided into two subgroups:
(1)Non-intenders A—patients who do not want to change their behaviors because they have the wrong idea about the relationship between lifestyles and illness (patients who answer “I do not believe it will make my health better” or “No particular reasons” to the question “Do you intend to change your behaviors in the next months?”). For non-intenders A, the tailored messages target patients’ outcome expectancies resulting from the change in behavior, focusing on positive effects and reducing negative outcomes.(2)Non intenders B—patients who do not want to change due to a lack of or low level of self-efficacy (I know I will never manage to do it). For this group, the tailored messages focus on self-efficacy, to improve patients’ perception that they can change and to reduce the cognitive barriers to change.Patients who have not (yet) set a goal to act (preintenders), but who might consider changing their behavior. For this group, the tailoring procedure is the same as non-intenders A.Patients who have set a goal to change their behavior but who are not yet acting (intenders). In this case, tailored messages present some real plans to implement the change, focusing on those plans the patients declare themselves unable to foresee. The social-cognitive predictors that will be addressed are action planning, which is the subject’s ability to identify real goals to put the change into action, and coping planning, which pertains to the anticipation of barriers that might arise during the acceptance and adoption of new behavior.Patients who already perform the behavior in question (actors). The tailored communication focuses on the possible obstacles that patients believe that they cannot overcome to maintain the new behavior. The social-cognitive predictors that will be addressed are maintenance self-efficacy and recovery self-efficacy. The former is about the subject’s confidence that he/she can maintain a difficult behavior, while recovery self-efficacy is about the subject’s belief he/she can resume a difficult behavior after an interruption.

Table 2 presents a summary of the tailoring scheme for the development of the tailored messages related to behavioral lifestyles.

